##### Chester Step Test (CST)

According to Sykes [48], the CST is a submaximal exercise test in which the individual has to go up and down a step at a controlled speed, according to a series of pre-recorded sound signals, for 10 min.

The CST is incremental, which means that at each step, the speed at which the individual has to go up and down increases (five steps of 2 min each). The metronome sets the cadence of the steps, which starts at step 1 (15 steps per minute) and progresses to step 2 (20 steps per minute), step 3 (25 steps per minute), step 4 (30 steps per minute), and step 5 (35 steps per minute). The choice of step height depends on the participant’s age, functional capacity, BP level, and body composition, ranging from 15 cm to 20 cm, 25 cm, and 30 cm. A height should be selected that allows the individual to comfortably reach level 3 of the test.

Two tests will be carried out by the same assessor (one experimental), with an interval of at least 30 min between them. HR will be recorded every two minutes using the Polar HR sensor. The perception of fatigue and SpO^2^ will be recorded at the end of each level, using the Modified Borg Scale and a MYCO OXI-200A finger oximeter, respectively. The CST ends when the participant reaches 80% of the reserve HR, using the equation (220-age) [49], if the SpO^2^ is below 85% or if the participant is unable to maintain the cadence of steps for 15 s. The test should be suspended if the participant’s perceived exertion is higher than 7, if they decrease their frequency as the level increases, and, after receiving positive reinforcement, do not react. If 80% of the reserve HR is reached halfway through a level, as long as there are no signs of discomfort, the test should continue.

#### 3.1.7. Heart Rate Monitoring

POLAR^®^ model V800 (Polar Electro Oy, Oulu/Finland) transmitters and cardiofrequency meters will be used to monitor HR. The cardiofrequency meter will be programmed to continuously monitor HR, placed on the chest, roughly at the level of the xiphoid apophysis of the sternum, and adjusted so that it does not fall off and so that it does not become uncomfortable during breathing. To facilitate data transmission, the sensor that is in contact with the skin should be covered with a small amount of gel beforehand. The receiver will be placed on the subject’s left wrist. Fifteen minutes before the start of the test, the signal will be received, and the resting HR will be recorded. The data from the HR recordings will then be transferred to the computer via an infrared interface.

The prescription of exercise intensity should be based on direct measurements of maximum HR, if possible, since an equation may not predict the true maximum HR in some individuals, in specific populations, or for certain types of exercise [50]. However, in individuals with ASD, direct measurements are difficult to obtain due to the behavioral characteristics of the population [30]. Therefore, in the present study, exercise intensity will be predicted indirectly using the following equation [51]:Maximum HR = 208 − (0.7 × age in years)(2)

The present study will use a methodology for managing the intensity of the effort, in which the exerciser with ASD performs physical effort in a range that oscillates between 50% and 80% of the maximum HR.

#### 3.1.8. Modified Borg Scale (MBS)

This scale is particularly useful in maximal/submaximal aerobic tests and exercise sessions. The MBS is a 10-point scale (0–10) which helps one to understand the intensity/severity of tiredness in less than 1 min [52]. During its application, the printed MBS (minimum font size 20) will be presented to the individual, and they will be asked to read all the possible levels. It will be explained that 0 means no fatigue at that moment, and 10 means the worst fatigue. The individual will then be asked to rate their feeling of fatigue at that moment based on the scale.

#### 3.1.9. Procedures

The intervention study involves seven phases: (i) The first is the design of the PE program. (ii) The second is the promotion of the [+ Life] program, where a poster will be distributed alluding to the importance of the practice of PA by the population under study, identifying the objectives under research, to be distributed by themselves/families/professionals who deal with this issue. A logo will also be created alluding to the whole process, making it the program’s brand image. (iii) The sample will be recruited: participants/parents/guardians will sign an informed consent form, and the entire project will be carried out in accordance with the Declaration of Helsinki [17,18]. (iv) The sample will be divided into the youth training group (YTG) and the adult training group (ATG). (v) An initial evaluation of the groups without blinding the evaluator will be conducted. (vi) A final evaluation of the groups without blinding the evaluator will be carried out. (vii) Data analysis will be performed: descriptive, comparison between groups, comparison before/after intervention, and correlations.

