## 2. Materials and Methods

### 2.1. Design of the Study

This protocol describes a non-randomized experimental study, following the Consolidated Standards of Reporting Trials statement [22], with the aim of evaluating the effectiveness of two combined physical capacities (aerobic capacity and muscular strength). Participants will be allocated to one of two groups: youth training (YT) or adult training (AT).

Participants will take part in a supervised PE program for 12 weeks, twice a week, for 90 min per session. All outcome measures will be collected at two different times, at baseline (time 0, baseline assessment, week 0) and at the end of the intervention (time 1, final assessment, week 12). Figure 1 shows the study design.

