### 2.5. Intervention Assignment and Blindness

Once the initial assessments have been completed, the volunteers will be allocated to the two groups according to their age group. Due to the nature of the intervention, it will not be possible to randomize the sample into groups nor to “blind” participants and the principal investigator.

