#### 3.1.6. Cardiorespiratory Fitness

##### Six-Minute Walk Test

This is a submaximal test, which aims to assess the distance an individual is able to walk for 6 min, in which two tests are required, with a minimum interval of 30 min between them. The usual medication and walking aids should be maintained. There should be no warm-up period. The individual should sit at rest in a chair, close to the starting position, for at least 10 min before the test begins. During this time, it should be checked whether the individual meets any of the contraindications for taking the test [47]. When it is implemented, the following will be recorded: peripheral oxygen saturation (SpO^2^), SBP, DBP, HHR, perceived dyspnea, and lower limb fatigue (Modified Borg Scale).

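### Both evaluations are declared unblinded, and nothing limits knowledge of baseline results or fixes encouragement, so evaluator expectation at week 12 can inflate walk distance and the judged parts of the step test

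*Protocol article*

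**What the plan says.** Section 3.1.9 (Procedures) fixes the evaluator's status at both assessments. For baseline: "An initial evaluation of the groups without blinding the evaluator will be conducted". For week 12: "A final evaluation of the groups without blinding the evaluator will be carried out".

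Section 2.5 gives a reason for the absence of blinding, but names only the participants and the principal investigator: "Due to the nature of the intervention, it will not be possible to randomize the sample into groups nor to “blind” participants and the principal" (the quote stops one word short of the end of the sentence). The article does not say who the evaluator is.

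Two tests depend on effort or on the evaluator's judgement:

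- The six-minute walk test (section 3.1.6), "which aims to assess the distance an individual is able to walk for 6 min". The article gives no rule on encouragement.
- The Chester step test (section 3.1.6). One ground for suspending it applies "if they decrease their frequency as the level increases, and, after receiving positive reinforcement, do not react". The evaluator also judges whether cadence has been lost and, once the heart-rate limit is reached within a level, whether there is discomfort.

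The Introduction hypothesises significant improvement in every assessed variable in each age group, and the Discussion expects the results to confirm benefit. The limitations in the Discussion name the lack of randomisation, the lack of a control group and uncontrolled activity outside the programme. They do not name unblinded evaluation.

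**The concern.** Everyone receives the programme and everyone is measured before and after it, so the evaluator cannot be masked to treatment and, in a live test, hardly to time point. Two things can still be controlled: whether the evaluator has a participant's baseline result to hand, and how much encouragement is given. The article controls neither.

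The direction of the risk is predictable. An evaluator who expects improvement may encourage more at week 12, or be slower to call lost cadence or discomfort. With no comparator, any such drift between week 0 and week 12 enters the change score in full and looks like a training effect. Hypotheses (i) and (ii), the within-group improvements, are the ones exposed. In the comparison of the two age groups under hypothesis (iii), a drift of equal size in both groups would cancel.

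The Discussion envisages use of the programme in institutions, schools or clinics if it proves effective, so an avoidable source of apparent benefit matters.

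**Working it through.** The plan states no figure on this point, so there is nothing to reproduce. The check has two parts.

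**1. Which outcomes are exposed**

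| Outcome | How it is obtained | Exposure to evaluator expectation |
|---|---|---|
| Six-minute walk distance | Effort-dependent; no rule on encouragement | Yes |
| Chester step test, level or time reached | Cadence set by recorded signals; numeric limits on heart rate, saturation, exertion and 15 s of lost cadence; reinforcement, loss of cadence and discomfort are judged | Partly |
| Waist circumference | Tape on skin at a defined landmark, read by the evaluator | To a lesser degree |
| Modified Borg rating | Rated by the participant on a printed scale with a set explanation | Little, through the evaluator |
| Heart rate, oxygen saturation, blood pressure, bioimpedance | Read by a device | Little |

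**2. How much a shift could matter**

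Inputs from the article: 18 participants (Abstract); Wilcoxon test between assessment times and p < 0.05 (section 3.1.11). Assumptions: an even split of 9 and 9, since the split is not stated; a two-sided test, since sidedness is not stated; normally distributed change scores with no true effect; and an evaluator-induced mean shift of b standard deviations of the change score.

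Rejection region at n = 9. There are 2^9 = 512 equally likely sign patterns under the null. Let W be the sum of the ranks opposing improvement.

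- W = 0: p = 2 × 1/512 = 0.0039
- W = 5: p = 2 × 10/512 = 0.039 (significant)
- W = 6: p = 2 × 14/512 = 0.055 (not significant)

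With no shift, the chance of a significant result in the direction of improvement is 10/512 = 0.0195, about 2%.

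With a shift b, simulation of the exact test (20,000 runs per cell) gives this chance of a falsely significant improvement:

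| Assumed shift b (SD of change) | n = 6 | n = 9 | n = 12 | n = 18 (both groups pooled) |
|---|---|---|---|---|
| 0 | 1.5% | 1.9% | 2.3% | 2.4% |
| 0.2 | 3.6% | 6.2% | 7.8% | 11.8% |
| 0.3 | 5.5% | 10.2% | 13.7% | 21.3% |
| 0.5 | 10.8% | 21.9% | 31.8% | 49.6% |

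The columns for 6 and 12 show an uneven split. The pooled column is for scale only, because hypotheses (i) and (ii) are stated by age group.

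The value p = 0.0039 needs all nine observed changes to point the same way, which a modest shift rarely produces. Under the same normal model the probability is Φ(b)^9: 0.618^9 ≈ 1.3% at b = 0.3, and 0.691^9 ≈ 3.6% at b = 0.5. The table is therefore the fair illustration, and the minimum attainable p-value is not.

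**The case against.** The strongest objection is that the article declares the lack of blinding openly, and that the handling of forms and the wording of encouragement are details a condensed article may leave to a fuller protocol or to the test manuals it cites. That stands in part. This is a weakness of a stated design choice, not a contradiction, and the cited manuals cannot be checked here. But unblinded evaluation is stated as the procedure, and no safeguard accompanies it.

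Several stronger readings are tempting and are not supported:

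- **That the week-12 evaluator sees baseline values.** The article never says so. It only does nothing to prevent it.
- **That one person assesses both visits.** The step-test sentence, "Two tests will be carried out by the same assessor (one experimental), with an interval of at least 30 min between them", concerns two tests about half an hour apart, not week 0 and week 12.
- **That section 3.1.9 extends non-blinding beyond its justification.** The evaluator may be the principal investigator, for whom section 2.5 does give a reason.
- **That every cardiorespiratory outcome is exposed.** Heart rate, saturation and blood pressure come from devices, most step-test limits are numeric, and reinforcement is mentioned only after the participant has already slowed.
- **That any shift, however small, gives p = 0.004.** That holds only if all nine observed changes share a sign.

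Two further objections carry weight. Withholding baseline sheets does not hide the time point, and expectation needs only the time point; fixed encouragement is the part of the remedy that addresses this. And the absence of a control group, which the article acknowledges, already prevents clean attribution of change to the programme. Evaluator expectation is one of several before/after explanations, but it is one that can be reduced at almost no cost.

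**Conclusion.** The concern holds in a limited form. Both evaluations are fixed as unblinded, nothing shown limits knowledge of baseline results or standardises encouragement, and the uncontrolled before/after design passes any evaluator drift straight into the measured change. The outcomes at risk are walk distance, the judged parts of the step test and, less so, waist circumference.

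The size is unknown, because the article gives no basis for it. Under the stated assumptions (9 per group, two-sided test, normal changes, no true effect), a shift of 0.2 to 0.5 SD raises the chance of a false improvement from about 2% to between 6% and 22% per outcome. These figures show sensitivity to an assumed bias and do not estimate one that is present. The change is worth making because it is cheap. The point does not invalidate the device-read outcomes.

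**What to change.** In section 3.1.9, state that:

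- the walk and step tests use the same fixed wording and timing of encouragement at both visits;
- week-12 results are recorded on fresh forms, with baseline results withheld from the evaluator until the week-12 data are locked, except for test settings such as step height, which are copied onto the form so that the two tests stay comparable.

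In the Discussion, add unblinded evaluation to the limitations and name the outcomes it chiefly affects. None of this alters the criteria for ending or suspending a test.

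The cost is procedure wording and a second set of forms, with no extra assessor, visit or measurement. The drawbacks are that the time point remains known, an evaluator may remember some baseline results in a sample of 18, and checks of plausibility against baseline can be made only after lock.

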#### 3.1.10. Predictable Risks

When starting a PE program, people who usually lead a sedentary lifestyle run the risk of feeling some kind of discomfort, fatigue, muscle pain, or even physical injury. Given that the intensity will be increased gradually, it is expected that muscle pain will be slight and brief, attenuated by the habit of stretching the muscles. Injury risk will be mitigated by the direct supervision of the research team in collaboration with professionals from the institution to which the sample belongs. In the event of physical injury, the necessary care will have to be provided to the participant, insurance will have to be taken out, and their inclusion in the project will depend on the consideration of all related parties.

Another inconvenience inherent to the intervention procedures may result in the appearance of symptoms associated with stress [30]. Such risks will be controlled or mitigated with the approach of the research team, in collaboration with the institution’s professionals, since the participants are already familiar with them. If necessary, a preferably playful approach will have to be taken to control the symptoms.

#### 3.1.11. Statistical Analysis

Descriptive parameters such as the mean and standard deviation will be used in the statistical analysis. The normality of the data will be checked using the Shapiro–Wilk test. Significant differences between groups will be analyzed using the Kruskal–Wallis test, while differences between assessment times will be investigated using the Wilcoxon test. The choice of non-parametric statistics is based on the central limit theorem, which suggests that in order to obtain a normal distribution, a minimum sample size of 30 participants is required [53]. The magnitudes of the differences will be assessed by Cohen’s d effect size [54]. In addition, associations between study variables will be checked using Spearman’s correlation coefficient [55]. The significance level adopted for all analyses will be *p* < 0.05. The data will be processed using the Statistical Package for the Social Sciences (SPSS) software, version 28, Chicago, IL, USA.

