## Abstract

**Background/Objectives**: Physical exercise (PE) has been shown to have positive effects on the symptoms associated with autism spectrum disorder (ASD). However, there is still no consensus on the most appropriate PE intervention model. With this in mind, we developed a program with the aim of determining the effects of PE on physical fitness, with a view to applying it as a potential treatment. **Methods**: Using an experimental methodology, this research work will recruit 18 institutionalized young people and adults who will be allocated to one of two groups, namely (i) the youth training group and (ii) the adult training group, using low-cost materials. Both intervention groups will perform 90 min of training per session, twice a week, for 12 weeks. Evaluations will be carried out at baseline and month 3. The impact of the exercise program will be assessed based on the variables of anthropometry, body composition, cardiovascular response, and cardiorespiratory fitness. **Results**: The results of this study will contribute to the development of more effective strategies, prescription recommendations, and interventions as a guarantee in future programs of better and greater adherence to PE by institutionalized individuals with ASD. **Conclusions**: In addition, we intend to make the PE program available if it promotes positive effects in the target population.

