Given the increasing prevalence of ASD and the lifelong nature of this condition, it has become imperative to address the health and well-being needs of this population throughout all stages of life. The transition to adulthood is a critical period, marked by significant changes that include a downward trend in the practice of physical exercise, which is widely documented in the literature [17,18,19]. In addition, physical exercise has been recognized as an effective non-pharmacological intervention to improve not only the physical condition but also the behavioral, social, and emotional aspects of people with ASD. To date, only three systematic reviews have included participants aged between 18 and 30 [19,20,21], highlighting a lack of data and clear guidelines for prescribing exercise programs that meet the specific needs of this population. Grouping young people and adults allows us to investigate how physical exercise can be an effective intervention to mitigate the challenges associated with this transition, promoting the maintenance of an active lifestyle.

The aim of this study was to evaluate the effects of a 12-week PE program on the anthropometry, body composition, cardiovascular response, and cardiorespiratory fitness of institutionalized young people and adults with ASD. The following hypotheses will be defined: (i) the youth group (YG) will display a significant improvement in all the variables assessed after a 12-week physical exercise program; (ii) the adult group (AG) will display a significant improvement in all the variables assessed after a 12-week physical exercise program; and (iii) one of the groups (YG or AG) will display a significantly greater improvement in all the variables assessed compared to the other group, after a 12-week physical exercise program.

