### 2.2. Participants

The program will involve volunteers, comprising young people and adults who are institutionalized in a care facility located in Coimbra (Portugal), recruited using the non-probabilistic convenience method. The YG will include individuals aged 10–17, and the AG will include individuals aged 18–65. This division is based on criteria widely recognized in the literature. Adolescence (10–17 years) is a critical phase of development characterized by rapid physiological and cognitive changes [23]. The adult age group (18–65 years), on the other hand, covers a wide range of stages, from early adulthood to middle age [24]. In the first stage, there will be an individual explanation of the objectives and procedures of the study, as well as the potential benefits, risks, and time required for its development. Secondly, participants/family members/legal guardians will sign an informed consent form.

The inclusion criteria will be as follows: (i) having a certified medical diagnosis of ASD (autistic disorder, Asperger’s syndrome, or pervasive developmental disorder without other specification) according to the standards established in the DSM-5-TR [1]; (ii) ages between 10 and 65 years; (iii) a recent history of non-participation in PE programs or similar physical motor activities; (iv) success in performing movements such as running, pulling, and pushing; (v) ability to perform the assessments; and (vi) attendance at least 75% of the total 24 sessions. The exclusion criteria will be defined as follows: (i) individuals who are unable to commit for 3 months; (ii) individuals with other associated pathologies; (iii) clinical contraindications; (iv) inability to walk without support; (v) inability to communicate; (vi) failure to provide signed informed consent; and (vii) individuals over the age of 18 who do not agree to take part in the study. Specific data on socio-economic status and level of education will not be recorded.

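### Hypothesis (iii) asks which age group improves more, but no stated analysis is said to compare the changes, so a baseline age difference could pass for a differential effect

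*Protocol article*

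**What the plan says.** The Introduction sets three hypotheses. The first two are improvement within the youth group (YG) and within the adult group (AG). The third is comparative: "one of the groups (YG or AG) will display a significantly greater improvement in all the variables assessed compared to the other group".

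Section 3.1.11 assigns one test to groups and another to times: "Significant differences between groups will be analyzed using the Kruskal–Wallis test, while differences between assessment times will be investigated using the Wilcoxon test". The last phase in section 3.1.9 lists the analyses in the same separated way: "descriptive, comparison between groups, comparison before/after intervention, and correlations". The article mentions no change score, group-by-time term or baseline adjustment.

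The groups are not randomized. Section 2.5 says that "the volunteers will be allocated to the two groups according to their age group", and section 2.2 gives the ranges: "The YG will include individuals aged 10–17, and the AG will include individuals aged 18–65". The Abstract gives a total of 18 participants; the split between groups is not stated. Outcomes are measured at week 0 and week 12 (section 2.1).

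**The concern.** Hypotheses (i) and (ii) are before/after questions, and a Wilcoxon test in each group fits them. Hypothesis (iii) concerns a difference between groups in the amount of change. To test it, the change itself has to be compared between groups.

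Read naturally, section 3.1.11 offers two routes to (iii), and neither is such a test:

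- **Kruskal–Wallis on week-12 values.** This compares levels. Adolescents and adults can be expected to differ before any exercise on some outcomes, most clearly body mass and lean mass. A group difference at week 12 may only repeat the difference at week 0.
- **Contrasting the two Wilcoxon results.** Finding significance in one group and not in the other does not test the difference between them. In groups this small it happens often when both respond equally.

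At stake is a conclusion that one age group responds better when both respond alike, or a real difference hidden by an opposite baseline gap.

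**Working it through.** The article gives no power, effect size, SD or correlation, so it has no figure to reproduce. The check is by simulation.

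**Inputs from the article:** total N = 18; two groups formed by age; two assessments; significance at p < 0.05 for all analyses.

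**Assumptions, not from the article:** two-sided tests; a split of 9 and 9; normal outcomes with baseline SD 1; the same true change in both groups, mean 0.3 and SD 0.5, independent of baseline; a baseline gap between groups of 0 to 2 SD.

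**Step 1. What the week-12 test sees.** The SD of a week-12 value is √(1² + 0.5²) = 1.118, which implies a pre/post correlation of 1/1.118 = 0.89. Because the true changes are equal, the whole baseline gap carries over to week 12. A gap of 1.0 SD at baseline is a standardized difference of 1.0/1.118 = 0.89 at week 12, with no differential effect.

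**Step 2. Rejection rates per variable when (iii) is false.**

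| Baseline gap (SD) | Kruskal–Wallis on week-12 values | Kruskal–Wallis on changes |
|---|---|---|
| 0 | about 6% | about 5% |
| 0.5 | about 15% | about 5% |
| 1.0 | about 42% | about 5% |
| 1.5 | about 73% | about 5% |
| 2.0 | about 93% | about 5% |

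A repeat with 10,000 trials per row agreed to within about one percentage point. A 6 and 12 split gave slightly lower week-12 rates, such as 39% at 1.0 SD and 90% at 2.0 SD. A separate model (change 0.5 SD, correlation 0.7 or 0.8) gave 45–50% at 1.0 SD and 95–97% at 2.0 SD, with 4.7–6.1% on changes.

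**Step 3. Contrasting two Wilcoxon tests.** If each group has the same power p, the chance that exactly one is significant is 2p(1 − p), which cannot exceed 50%. With n = 9 per group and a common paired effect dz (mean change divided by SD of change):

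| dz | Exactly one group significant |
|---|---|
| 0.3 | about 20% |
| 0.6 | about 42% |
| 0.8 | about 50% (p = 0.487; 2 × 0.487 × 0.513 = 0.50) |
| 1.2 | about 28% |
| 1.5 | about 9% |

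The model in Step 2 has dz = 0.3/0.5 = 0.6.

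**Step 4. The opposite error.** Take 9 per group, correlation 0.8, a true difference in change of 1 SD and a baseline gap of 1 SD in the other direction. The week-12 test rejects in 4.8% of trials; the test on changes rejects in 85.6%.

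**Step 5. What the right comparison can deliver.** For a difference between groups of 1.0 SD of change, with 9 per group, the normal approximation gives power Φ(1.0 × √(9/2) − 1.96) = Φ(0.16) = 56%. Power of 80% needs 2 × (1.96 + 0.84)²/1.0² = 15.7, so 16 per group.

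**The case against.** A reader might infer that the plan never compares changes and cannot answer (iii). The text does not go that far. Section 3.1.11 does not name the quantity that enters the Kruskal–Wallis test, and running that test on week 12 minus baseline would fit the sentence and answer (iii). A condensed article may also leave the dependent variable of each test to a fuller document. This stands as a limit on the claim. It does not remove the point, because the article does fix the tests, and both places that list them keep the group comparison apart from the before/after comparison. The reading that gives a wrong answer is therefore the natural one.

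The other objections concern size and tone, and most hold:

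- The split, SDs and baseline gaps are assumptions. With no gap the week-12 test is close to its nominal level, and at 0.5 SD it rejects in about 15%. A gap of 1 SD or more is plausible for body mass, but the article does not support it for resting heart rate, blood pressure or walking distance. Adults span 18–65, so their mean is hard to predict.
- The 50% figure for discordant Wilcoxon results is the ceiling of 2p(1 − p), and the article does not say that it will draw inferences from such a contrast.
- The rates are per variable. Hypothesis (iii), taken literally, requires greater improvement in every variable, so falsely confirming it in full is far less likely.
- Using Kruskal–Wallis with two groups is not a fault. It is equivalent to the Mann–Whitney test.
- The article calls the work a pilot and discloses the lack of randomization and of a control group. It still states (iii) as a hypothesis about significance, with one threshold for all analyses.

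**Conclusion.** The point holds in a limited form. Hypothesis (iii) is about differential change, and the article does not say that any planned test compares changes. If the between-group test is run on week-12 values, its error rate for (iii) depends on the baseline gap between age groups: per variable, from about 6% with no gap to about 42% at 1.0 SD and 93% at 2.0 SD, against about 5% on changes. If the two Wilcoxon results are contrasted, exactly one is significant in roughly 10–50% of trials with equal true effects. These figures rest on the assumed 9 and 9 split, equal true changes and the stated SDs. The mechanism does not depend on those values, but a gap near zero removes most of the excess for the week-12 test.

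Comparing changes removes the error from baseline levels only. A difference in change between ages 10–17 and 18–65 may still reflect growth, maturation or regression to the mean, and no analysis of these data can separate these from the program without a control group.

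**What to change.** In section 3.1.11, add wording to this effect:

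1. Hypothesis (iii) is tested on each participant's change, week 12 minus baseline, with one two-group rank test (Mann–Whitney, equivalent to Kruskal–Wallis here). The Hodges–Lehmann difference between groups is reported with its 95% CI. A baseline-adjusted or group-by-time model would be an acceptable alternative if named in advance.
2. Baseline differences between the groups are described, not tested.
3. Significance in one group only is not taken as evidence of a difference between groups.
4. Without a control group, a difference in change may reflect growth, maturation or regression to the mean.

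Both assessments are already planned for every participant, so no extra data are needed and only the analysis wording changes. Power for (iii) stays modest at this sample size, so the interval should carry more of the interpretation than the p-value.
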